## Abstract

This study aims to test the effectiveness of a community-based intervention (Konga model) to improve viral-load suppression in children living with human immunodeficiency virus (HIV) and enrolled in care and treatment centers in Tanzania mainland. The study will be a cluster-randomized clinical trial study designed with both intervention and control arms. The study will involve 268 children with a viral load of >1000 copies/ml who are aged between 2 and 14 years. The children will be randomly allocated into the intervention and control arms. The intervention will include three distinct activities: adherence and retention counseling, psychosocial support, and comorbidity screening (i.e. tuberculosis). The outcome of the study will be assessment of the success of the intervention to increase medication adherence with the immediate result of reducing the viral load below 1000 copies/ml. Descriptive statistics will be used to calculate the mean, median, standard deviation, and interquartile range of continuous data. We will use frequencies and percentages to summarize categorical data. As for the primary outcome (proportion of HIV-infected children with viral suppression), we will compare the proportion of successful participants in the intervention and control arms. Proportions and tests for different proportions will be used as a measure of improvement. All statistical tests will be two-sided and *P* < 0.05 will be considered statistically significant.

## Introduction

The retrovirus human immunodeficiency virus (HIV) attacks the body’s cellular immune system and acquired immunodeficiency syndrome (AIDS) can eventually result [1]. The attack depletes CD4 cells, which leaves people vulnerable to illnesses that a healthy immune system would otherwise eliminate [2–4]. Retroviral infection remains the leading cause of morbidity and mortality throughout the world [5]. However, with the introduction to antiretroviral therapy (ART) and wide accessibility, mortality has been significantly reduced [6–8]. Thus, HIV infection has become a manageable chronic health condition, enabling people living with HIV (PLHIV) to live long and quality healthy lives [9].

Viral-load measurement emerged as an essential monitor of a therapy’s effectiveness after ART initiation and it is considered a surrogate marker for disease progression [3, 10]. ART in children aims to suppress HIV replication and halt disease progression while reducing opportunistic infections and morbidities [11, 12].

Viral-load suppression (VLS) after early ART initiation is the primary goal in children [13]. Globally, about 400,000 children living with HIV under 15 years of age who are receiving ART and living in low- and middle-income countries have not achieved VLS [14]. In East-African nations, compared with other countries in sub-Saharan Africa, a low proportion of children on ART achieved VLS [15, 16]. Thus, there is high risk of developing AIDS. In Tanzania, program data and the Tanzania HIV Impact Survey (THIS) have demonstrated that VLS in pediatric patients continues to be low [4, 17, 18].

Several studies have cited factors causing unsuppressed viral loads, such as poor adherence and co-morbidities [14, 19, 20], malnutrition [21, 22], and underlying tuberculosis (TB) infection [23]. These patients who initially received ART still have advanced disease [24].

Despite substantial ART coverage in other groups living with HIV in Tanzania, the VLS among HIV-positive children on ART remains unacceptably low at 18%. That means that 82% of those enrolled in care and treatment centers (CTCs) and receiving ART did not achieve VLS [4]. Several studies have demonstrated that early enrollment of children to ART and maintaining good adherence (retention) reduces HIV replication and suppresses the virus [25, 26]. Through the National HIV/AIDS Control Program, the Government of Tanzania has made efforts to improve retention and adherence for PLHIV. These efforts have not however been effective for VLS among children due to the loss of follow-up of caregivers and their HIV-exposed infants [27].

Trials in different countries have demonstrated that community-based intervention improves HIV care services among children living with HIV and AIDS [25, 28–30]. Thus, UNAIDS [31] recommends a requirement of sustained engagement and unique inputs from various communities, from small informal groups at the grassroots level up to global coalitions.

We therefore identified the need for a sustainable intervention that promotes retention and adherence to ART and that addresses low VLS among children living with HIV in Tanzania.

## Material and methods

### Study area

We will conduct this study in the Simiyu Region. Administratively, the region is comprised of six district councils with a total of 218 health facilities (8 hospitals, 17 health centers, and 193 dispensaries), of which 106 sites provide ART.

### Study design and population

We will use a cluster-randomized trial study designed with both intervention and control arms. The study will involve 268 children (134 controls and 134 patients who receive intervention) aged 2–14 years who are attending CTC and who have a viral load of >1000 copies/ml.

### Recruitment

The healthcare workers (i.e. ART nurses) will identify and recruit children with a viral load of >1000 copies/ml and who were aged 2–14 years. Before recruitment, informed consent will be obtained from their caregivers.

### Intervention

The UNAIDS and previous studies have recommended the engagement of communities, from small informal groups at the grassroots level up to global coalitions, to improve HIV care [31]. The National Council of PLHIV (NACOPHA) is a non-profit, non-government organization. It is a national grassroots-based organization of all individuals who are recognized through organized groups and clusters of PLHIV in Tanzania mainland. Since its establishment has embarked upon coordinating the efforts of PLHIV through their district clusters known as “Konga” to address the needs of PLHIV. Konga is a Swahili name meaning that is a Cluster of PLHIV at the district level, thus Konga is the smallest unit of NACOPHA. Hence, we will use the community of PLHIV known as Konga to provide services to children.

### Plan for the intervention

#### Role of the health worker

The health workers, usually the ART nurses at the selected facility, will identify children with low VLS and link them to the Konga. They will also continue routine care of the child.

#### Roles of the Konga

We will provide the standard operating procedures (SOPs) to the Kong such that different person will use for the provision of the desired intervention. The SOP will have specific standards adapted from the National HIV care and treatment guidelines, thus the Konga will use the SOP:

To provide enhanced adherence counseling and intensive follow-up. Here, the Konga will routinely visit the client’s house and at every visit they will assess and document:∘ Medication regimen, storage of drugs at home.∘ Doses missed: how often, why, then solve problem with the client.∘ Side effects such as headache, nausea and vomiting, diarrhea, fatigue, sleeping, difficulty, a dry mouth, a rash, dizziness and a pain and client response.∘ Use of other medications, including traditional medicines.∘ Challenges.Follow-up screening for TB and other comorbidities (members of the Konga will visit the children and screen for opportunistic infection and encourage them to visit the health facility for further management); andProvision of psychosocial support by members of the Konga team.

### Outcome measures

The study will have two outcome measures. The primary measure will be the adherence, this will be measured by using the standard adherence tool (National AIDS Control Program [32]) and loss to follow-up (retention in CTC), which will be compared in both arms. We will measure these metrics at baseline, subsequent follow-up, and the study’s end (i.e. 6 months). The secondary measure will be the viral load, which will be measured at the baseline and subsequently at the 6-month study’s end, comparing both arms.

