### Sample size calculation and selection

The trial will be conducted in 20 CTC clinics that deliver HIV care and treatment within the four selected districts (10 CTCs will carry out the intervention and 10 CTCs will carry out standard care). We determined the study size from the primary outcome of proportional HIV-positive children with a viral load >1000 copies/ml. According to THIS (2018), 18% of HIV-positive children under the age of 15 years had a viral load >1000 copies/ml; thus, we assumed that value for standard care. Therefore, under a cluster design, the study will need a total sample size of about 268 children (134 in the intervention group and 134 in the control group) to increase the proportion of children with viral suppression from 18% to 30% with 80% power, ata5% significance level, an intra-cluster correlation of 0.01, and 10% expected loss to follow-up. We carried out this power calculation using the Stata™ function “clustersampsi” command (clustersampsi, binomial p1[0.18] p2[0.3]k[20] rho[0.01] alpha[0.05] beta[0.8]).

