**Figure 1: bpac002-F1:**
[figure not shown]
study design and flow chart.

The study will be open-label whereby the Konga, caretakers, and the children will be aware of the intervention received since neither the outcome assessor nor person receiving the intervention will influence the outcome. The study’s primary outcome is to reduce the viral load <1000 copies/ml.

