### Data processing and analysis

We will enter data into Excel™ software and analyze it using Stata™ software. Descriptive statistics will summarize continuous data, such as the mean, median, standard deviation, and interquartile range. We will use frequencies and percentages to summarize categorical data. Multiple statistical tests and methods will be employed. The univariate analysis will typically utilize Pearson’s chi-squared correlation or Fisher’s exact test, where appropriate. As for the primary outcome (mean difference in the viral load of HIV-positive children with VLS), we will use an independent *t*-test to compare the means of participants in the intervention and control arms. We will develop a multivariable regression model, adjusting for clustering and other confounders for potential confounding. We will use proportions and tests for different proportions as measures of improvement using the difference in difference. All statistical tests will be two-sided and *P* < 0.05 will be considered statistically significant.

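### The protocol names three different primary outcomes, and those in its outcome and analysis sections are not the one used for the sample size

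*Protocol article*

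**What the plan says.** The protocol article describes its primary outcome in five sections, in three ways.

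- **Adherence with retention.** Outcome measures: "The primary measure will be the adherence, this will be measured by using the standard adherence tool", continuing "and loss to follow-up (retention in CTC), which will be compared in both arms". The same section then says "The secondary measure will be the viral load".
- **Binary viral load at 1000 copies/ml.** Abstract: "As for the primary outcome (proportion of HIV-infected children with viral suppression". Sample size calculation and selection: "We determined the study size from the primary outcome of proportional HIV-positive children with a viral load >1000 copies/ml"; this is worded as non-suppression, but the calculation that follows is for suppression rising from 18% to 30%. Text after Figure 1: "primary outcome is to reduce the viral load <1000 copies/ml". The Dependent variable section agrees, classifying viral load as suppressed or unsuppressed at the same threshold.
- **Mean viral load.** Data processing and analysis: "As for the primary outcome (mean difference in the viral load of HIV-positive children with VLS", to be compared between arms by an independent t-test.

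**The concern.** These are different endpoints on different scales with different tests. The Outcome measures section expressly makes secondary what three other sections call primary. The analysis section attaches the word primary to a quantity that no other section calls primary.

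If this stands, the published text allows more than one answer to whether the trial met its primary outcome. A trial in which recorded adherence improved but viral suppression did not would be positive under Outcome measures and negative under the Abstract. The choice could be made after the results are known, and the stated two-sided 5% level would then not describe the chance of a false claim.

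**Working it through.** **1. Which outcome was sized.** The sample-size section gives suppression of 18% against 30%, 80% power, 5% significance, intra-cluster correlation 0.01, 10 clinics per arm, 10% loss, and a total of 268 (134 per arm). The analysis section makes all tests two-sided. The inputs are two proportions, so the calculation concerns binary suppression. No rate, standard deviation or effect size is given for adherence, retention or mean viral load.

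Reproducing the figure:

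- Individual randomisation: n = [1.96√(2 × 0.24 × 0.76) + 0.8416√(0.18 × 0.82 + 0.30 × 0.70)]² / 0.12² = (1.184 + 0.503)² / 0.0144, about 198 per arm.
- With k = 10 clusters per arm: nk(1 − ρ)/(k − nρ) = 198 × 10 × 0.99 / (10 − 1.98) = 244.4 per arm, 489 in total; 489/0.9 = 543 after loss.
- Reading the k of 20 in the quoted Stata command as clusters per arm: 217.6 per arm, 435 in total before loss.
- Power at 134 per arm (13.4 per clinic): design effect 1 + 12.4 × 0.01 = 1.124; effective size 134/1.124 = 119.2; power about 58%. After 10% loss (120.6 per arm, design effect 1.1106, effective size 108.6), about 54%.

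The figure of 268 is not reproduced. That is a separate problem. Here the step shows only that suppression is the outcome used for the sample size, not that the trial has adequate power for it.

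**2. The sections side by side.**

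| Section | Outcome called primary | Used for sample size? |
|---|---|---|
| Abstract | Proportion suppressed | Yes |
| Outcome measures | Adherence with loss to follow-up | No |
| Sample size | Binary at 1000 copies/ml | Yes |
| Text after Figure 1 | Viral load below 1000 copies/ml | Yes |
| Data processing and analysis | Mean viral load, t-test | No |

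The two rows marked No are the section that should define the outcome and the section that should analyse it.

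**3. Two further signs of the conflict.** The Independent variable section lists adherence among the independent variables, although Outcome measures makes it the primary outcome. The open-label justification after Figure 1 rests on nobody being able to influence the outcome. That is arguable for a laboratory viral load and much harder to sustain for missed doses recorded in an unblinded trial of adherence counselling.

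**4. The analysis wording taken literally.** Every child enters above 1000 copies/ml, so children with suppression form a group defined after randomisation. At the planning rates that group is 0.18 × 134 = 24 control and 0.30 × 134 = 40 intervention children, no longer comparable by randomisation. All of them are below 1000 copies/ml by definition, so the comparison of means would not measure the planned gain from 18% to 30%.

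**5. Size of the error-rate effect.** For three candidates each tested at 5%, the chance of at least one false positive under independence is 1 − 0.95³ = 14.3%. Suppression and mean viral load come from the same 6-month assay, and adherence is the intended route to suppression, so the tests are not independent. The document gives nothing from which to estimate the true figure. All that can be said is that it exceeds 5% if the primary is chosen after the data are seen.

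**The case against.** The best defence is that the intended primary can be inferred. Binary suppression is primary in the Abstract and after Figure 1, is the basis of the sample size, and is the dependent variable; Outcome measures and the analysis section are the outliers. This stands as far as it goes. A reader might infer that the trial has no primary hypothesis at all, and the document does not support that. It supports a contradiction, located in the two sections where it does most harm.

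A second defence is that a journal article condenses a fuller protocol and that an analysis plan may exist. Condensation explains omissions; it does not explain current text that names different outcomes as primary.

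Other stronger readings also fail:

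- A reader might infer that adherence and retention have no planned analysis. Outcome measures says they will be compared between arms, and the analysis section lists chi-squared, Fisher and proportion tests that could cover them. Further detail may properly sit in an analysis plan. The missing effect size for adherence simply follows from sizing on suppression.
- A reader might count adherence and retention separately and quote 1 − 0.95⁴ = 18.5%. The document describes them under one primary measure, and independence fails in any case.
- A reader might infer that the registry entry is wrong. Only its number is given, so its wording cannot be judged.

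**Conclusion.** The finding holds as an internal contradiction that must be resolved. Three incompatible primary outcomes stand in current text, and the ones in the outcome and analysis sections both differ from the one used for the sample size. The main harm is qualitative: the same data can be declared a success or a failure depending on the section cited. The inflation above 5% applies if the choice is made after results are seen, and its size cannot be fixed from the document. The literal reading of the analysis section, restricted to suppressed children, may be loose wording, but as written it names a comparison that randomisation does not protect.

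**What to change.** Before outcome data are seen, state one primary outcome in the Abstract, Outcome measures, Sample size calculation and selection, the text after Figure 1, and Data processing and analysis: the proportion of all enrolled children with viral load below 1000 copies/ml at 6 months. In the sample-size section, word it as suppression throughout. In the analysis section, replace the t-test among suppressed children with a between-arm comparison of that proportion that accounts for clustering by clinic. List adherence, retention and log10 viral load in all enrolled children as secondary. Check that the registry entry agrees.

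The cost is a change of wording. Viral load at 6 months is already to be collected in both arms, so no new data are needed. The change leaves the sample size of 268 unresolved; it needs its own recalculation and should not be taken as validated by naming suppression as the primary.

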### Sample size calculation and selection

The trial will be conducted in 20 CTC clinics that deliver HIV care and treatment within the four selected districts (10 CTCs will carry out the intervention and 10 CTCs will carry out standard care). We determined the study size from the primary outcome of proportional HIV-positive children with a viral load >1000 copies/ml. According to THIS (2018), 18% of HIV-positive children under the age of 15 years had a viral load >1000 copies/ml; thus, we assumed that value for standard care. Therefore, under a cluster design, the study will need a total sample size of about 268 children (134 in the intervention group and 134 in the control group) to increase the proportion of children with viral suppression from 18% to 30% with 80% power, ata5% significance level, an intra-cluster correlation of 0.01, and 10% expected loss to follow-up. We carried out this power calculation using the Stata™ function “clustersampsi” command (clustersampsi, binomial p1[0.18] p2[0.3]k[20] rho[0.01] alpha[0.05] beta[0.8]).

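### The 18% planning rate is called unsuppressed in one sentence and used as suppressed everywhere else, and it is not shown to be the 6-month suppression rate in the control arm

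*Protocol article*

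**What the plan says.** All references are to the protocol article.

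- **Introduction:** "the VLS among HIV-positive children on ART remains unacceptably low at 18"%, followed by the complement: "82% of those enrolled in care and treatment centers (CTCs) and receiving ART did not achieve VLS". Here 18% is the suppressed share.
- **Sample size calculation and selection:** citing the 2018 national survey, "18% of HIV-positive children under the age of 15 years had a viral load >1000 copies/ml"; "thus, we assumed that value for standard care". Under the definition in the Dependent variable section, a count above 1000 copies/ml is unsuppressed, so here 18% is the unsuppressed share.
- **Same paragraph, next sentence:** the trial is sized "to increase the proportion of children with viral suppression from 18% to 30% with 80% power". The Stata command quoted there has p1 = 0.18 and p2 = 0.3. Here 18% is suppressed again.
- **Study design and population:** the children are those "who are attending CTC and who have a viral load of >1000 copies/ml". The Abstract and the Recruitment section give the same criterion.
- **Outcome measures** and **End of study:** viral load is measured at baseline and at 6 months.

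**The concern.** There are two separate problems with one number.

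First, its meaning flips. The sample size section introduces 18% as the share with a high viral load, then uses it as the share suppressed. A reader cannot tell from that paragraph what the survey reported.

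Second, whichever way the survey figure reads, it is a cross-sectional prevalence among HIV-positive children (on the Introduction's account, those on ART and enrolled in care). Such a group includes children who are already suppressed. The trial excludes them. The planning quantity it needs is the share of initially unsuppressed children who are suppressed 6 months later on standard care. The protocol carries the prevalence over as the standard-care rate and offers no argument that the two are alike.

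The sample size, the stated power and the target of 30% all start from this figure.

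**Working it through.** **1. Does the contradiction reach the calculation?**

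The Introduction, the 18%-to-30% target and the command inputs all treat 18% as suppressed. The sentence citing the survey does not, and the sentence before it also frames the outcome as the share above 1000 copies/ml.

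The planned contrast itself does not depend on which way the outcome is labelled. Suppressed, 18% v 30%: 0.18×0.82 + 0.30×0.70 = 0.3576. Unsuppressed, 82% v 70%: 0.82×0.18 + 0.70×0.30 = 0.3576. The variance and the difference are the same, so n is the same.

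Only if the literal sentence were true of the control arm (82% suppressed) would the number change. A 12-point gain would then be 82% to 94%, a target that the protocol never states: n = 111.2 per arm before clustering, and about 79% power with the planned numbers.

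**2. Reproducing the plan's figure**

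Inputs (Sample size section; two-sidedness from Data processing and analysis): p1 = 0.18, p2 = 0.30, two-sided 5%, 80% power, ICC ρ = 0.01, k = 10 clinics per arm, 10% loss.

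- Before clustering: n = (1.960 + 0.842)² × 0.3576 / 0.12² = 7.849 × 0.3576 / 0.0144 = 194.9 per arm (197.7 with a pooled variance).
- Children per clinic with k fixed: m = n(1−ρ)/(k−nρ) = 194.9×0.99/(10−1.949) = 23.97, so 24 per clinic and 240 per arm.
- After loss: 240/0.9 = 267 per arm.

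The stated 134 per arm does not reproduce. The stated total of 268 is close to the size of one arm. This is a separate defect, noted so that it is not charged to the present point.

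**3. Sensitivity to the control rate**

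Power of 134 per arm: evaluable 134×0.9 = 120.6; per clinic 12.06; design effect 1 + 11.06×0.01 = 1.111; effective n = 120.6/1.111 = 108.6 per arm. Power = Φ(0.12/SE − 1.960), with SE = √{[pC(1−pC) + pT(1−pT)]/108.6} and pT = pC + 0.12.

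At 18%: SE = √(0.3576/108.6) = 0.0574; 0.12/0.0574 = 2.091; Φ(0.131) = 0.552.

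| Control rate | n per arm before clustering | n per arm, clustered and after loss | Power of 134 per arm |
|---|---|---|---|
| 5% (assumed) | 102.8 | 134 | 82% |
| 10% (assumed) | 142.6 | 189 | 69% |
| 18% (protocol) | 194.9 | 267 | 55% |
| 30% (assumed) | 247.2 | 367 | 46% |
| 50% (assumed) | 264.7 | 400 | 43% |

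**4. Sensitivity to the effect scale**

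Holding the gain at 12 points is itself an assumption. The protocol's contrast is an odds ratio of (0.30/0.70)/(0.18/0.82) = 1.95. If that were held constant instead, power (pooled-variance test, which gives 54% at 18%) would be about 23% at 5%, 38% at 10%, 66% at 30% and 68% at 50%. The pattern reverses.

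**The case against.** The best defence is that the flip is a slip of wording. The Introduction, the target and the command inputs agree on 18% suppressed, and relabelling the outcome leaves n unchanged. That stands: the contradiction alone changes no planned number, and a reader who inferred from it that the calculation ran on the wrong proportion would go beyond the text.

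The second defence is that 18% may still be right. The documents give no 6-month rate for children on standard care, so 18% could be correct by coincidence. That also stands. A reader might infer that 18% is the wrong control rate, or that it is too low and the trial loses power because of it. The documents support neither. Since every child starts unsuppressed, a rate below 18% is as open as one above it, and at 5% with a 12-point gain the planned 134 per arm would be adequate.

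A reader might also put the whole gap between 55% and 80% power down to this figure. That gap is present with 18% taken at face value; it arises because 134 per arm does not follow from the protocol's own inputs.

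What the defence does not answer is that two statements in the protocol cannot both be true, and that the main planning input is carried over from a differently selected group without justification. A fuller protocol or analysis plan could supply a justification, but it could not make both sentences true.

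**Conclusion.** The point holds in two parts.

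1. The survey sentence in the sample size section contradicts the Introduction and the calculation beside it. Which reading the survey supports cannot be settled from the documents.
2. The 18% is a prevalence among HIV-positive children not selected for viral load. It is not shown to be the proportion of initially unsuppressed children who suppress by 6 months on standard care.

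The size of the second part is a range, not a one-way loss. For a 12-point gain, power with 134 per arm runs from about 82% (control rate 5%) to 43% (50%), and the number needed from 134 to 400 per arm. This rests on ICC 0.01, 10 clinics per arm, 10% loss, a normal approximation and assumed control rates other than 18%. The direction of any error is unknown and depends also on the effect scale. Correcting the sample size arithmetic without grounding the control rate would still leave the resulting number unsupported.

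**What to change.** - Check the survey source and correct the sentence in the sample size section so that it agrees with the Introduction and with the calculation. If the source supports the other reading, the Introduction and the calculation must be revised instead.
- Base the control assumption on 6-month re-suppression among children with a viral load above 1000 copies/ml on standard care. The CTC2 database, for which the trial already plans to seek permission, is a natural place to look, provided that it holds repeat viral loads; the protocol does not say whether it does. If it does not, label 18% plainly as an assumption.
- Restate the power of 134 per arm for control rates on both sides of 18% (for example 5%, 10%, 18%, 30% and 50%), and say whether the effect is held fixed as a difference or as an odds ratio.
- Treat the failure of 134 per arm to follow from the stated inputs as its own correction.

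The cost is a rewritten paragraph and, where the data exist, an extraction from program records. The downside is that the stated power may become less favourable.

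### 134 children per arm give about 50–55% power for 18% versus 30%, not the stated 80%; the total of 268 is close to a per-arm requirement

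*Protocol article*

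**What the plan says.** The section Sample size calculation and selection of the protocol article sets the target "to increase the proportion of children with viral suppression from 18% to 30% with 80% power". It adds a 5% significance level, an ICC of 0.01 and 10% expected loss to follow-up. It concludes that "the study will need a total sample size of about 268 children (134 in the intervention group and 134 in the control group"). Twenty clinics take part: "10 CTCs will carry out the intervention and 10 CTCs will carry out standard care". The Stata command is printed with the arguments "binomial p1[0.18] p2[0.3]k[20] rho[0.01] alpha[0.05] beta[0.8"].

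The section Study design and population repeats the figure: "The study will involve 268 children (134 controls and 134 patients who receive intervention"). The Abstract also gives 268 as the number of children in the whole study. The section Data processing and analysis fixes the sidedness: "All statistical tests will be two-sided".

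**The concern.** The sample size section gives every input needed to recompute the number, and the inputs and the output disagree. The count of 134 per arm is lower than the number for an individually randomised trial with complete follow-up. Clustering with a positive ICC and loss to follow-up can only raise the requirement, so the discrepancy cannot come from how either was handled.

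At stake is the trial's central quantitative claim. If the claim is wrong, the trial has roughly an even chance of detecting the effect it was sized for, while its readers are told the chance is four in five. A non-significant result would then say much less about the Konga model than the stated power implies.

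**Working it through.** **Inputs.** From the sample size section: p1 = 0.18, p2 = 0.30, power 0.80, α = 0.05, ICC ρ = 0.01, loss 10%, 10 clinics per arm, 134 children per arm. From the analysis section: two-sided tests.

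**Step 1. Individual randomisation, no loss.** The variance sum is 0.18 × 0.82 + 0.30 × 0.70 = 0.1476 + 0.2100 = 0.3576.

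n = (1.96 + 0.8416)² × 0.3576 / 0.12² = 194.9, so 195 per arm. The version with pooled variance under the null gives 197.7, so 198 per arm. Both exceed 134.

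**Step 2. Add clustering with a fixed number of clusters.** For k clusters per arm, the number per cluster is m = n(1 − ρ) / (k − nρ).

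- k = 10: m = 194.9 × 0.99 / (10 − 1.949) = 23.97, so 24 per clinic and 240 per arm.
- k = 20 (if the value in the command means clusters per arm): m = 10.7, so 11 per clinic and 220 per arm.

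**Step 3. Add 10% loss.** 240 / 0.9 = 266.7, so 267 per arm (534 in total). With k = 20: 220 / 0.9 = 244 per arm.

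A t reference distribution with 2(k − 1) degrees of freedom asks for more. For k = 10 it needs 28 per clinic, which is 280 per arm or 311 enrolled. For k = 20 it needs 12 per clinic, which is 240 per arm or 267 enrolled.

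**Step 4. Attempt to reproduce 134 per arm.** One-sided tests, a continuity correction, pooled and unpooled variance, k = 10 or 20 per arm, and with or without clustering and loss were all tried. None gives 134 per arm at 80% power for 18% versus 30%.

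**Step 5. Power of the stated design.** Evaluable per arm: 134 × 0.9 = 120.6. Per clinic: m = 12.06. Design effect: 1 + 11.06 × 0.01 = 1.111. Standard error: √(0.3576 × 1.111 / 120.6) = 0.0574. Ratio: 0.12 / 0.0574 = 2.09. Power: Φ(2.09 − 1.96) = 0.55; with the noncentral t on 18 degrees of freedom, 0.51.

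Two-sided power for 134 enrolled per arm (unpooled variance):

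| Setting | Normal | t |
|---|---|---|
| 10 clusters per arm, 10% loss | 55% | 51% |
| 10 clusters per arm, no loss | 59% | 55% |
| 20 clusters per arm, 10% loss | 58% | 55% |
| 20 clusters per arm, no loss | 62% | 60% |
| No clustering, no loss | 64% | – |

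The pooled-variance formula gives values about one point lower (54% instead of 55% in the first row). A simpler central-t approximation gives 50% in that row.

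**Step 6. Detectable effect.** With 120.6 evaluable per arm, 10 clusters per arm and ICC 0.01, 80% power is reached for a rise from 18% to about 34.5% (normal) or 35.5% (t).

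**Step 7. Reading 268 as per arm.** With 268 × 0.9 = 241.2 evaluable per arm and 10 clusters per arm, power is 80% (normal) or 76% (t).

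**The case against.** No reading was found that rescues the 80%. The most favourable one (one-sided, no clustering, no loss) gives only 75%, and the analysis section excludes one-sided tests. The fair objections concern the surrounding claims.

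- **The origin of 268 is unknown.** The printed command has k = 20. Under the normal approximation, 20 clusters per arm leads to 244, not 268. The match at 267 arises with k = 10 (normal) or with k = 20 (t). This stands: the mislabelling is a plausible explanation, not a demonstrated one. The power shortfall does not depend on it.
- **The meaning of k is not stated.** It could be clusters per arm or in total. This also stands as a point for the authors to clarify. Both readings require far more than 134 per arm.
- **267 per arm is not the only correct value.** With 10 clinics per arm and a t reference, 311 enrolled are needed. This stands, so the total requirement is best given as a range of roughly 530 to 620.
- **The 50–55% assumes the full 10% loss and 10 clusters per arm.** Across readings of k and loss, two-sided power at ICC 0.01 runs from about 50% to 62%, still well short of 80%.

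Two further objections do not help. The section attaches the 18% both to a viral load above 1000 copies/ml and to suppression, but 18% versus 30% has the same variance as 82% versus 70%. An analysis plan that is not shown could not make the printed inputs and output agree.

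**Conclusion.** The concern holds. On the plan's own inputs, 134 children per arm give about 50–55% power for 18% versus 30%, against the 80% stated. The requirement under those inputs is about twice the stated total: roughly 534 enrolled under the normal approximation and about 620 with a t reference on 18 degrees of freedom.

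The 50–55% rests on an ICC of 0.01, equal cluster sizes, 10 clinics per arm and 10% loss. The ICC is the plan's own value. If it were 0.05, which is an assumption made here for illustration, power after loss would fall to 42% (normal) or 39% (t). The conclusion that 80% is not reached needs none of these assumptions, because 134 is below the 195 to 198 per arm required without clustering or loss.

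**What to change.** In the sample size section, replace the 80% claim with the power that 134 per arm provides: about 50–55% for 18% versus 30% after 10% loss. Equivalently, state that 80% power is reached only for a rise from 18% to about 35%. Rerun the command with 10 clusters per arm, say whether its cluster argument is per arm or in total, and show the 10% inflation as a separate line. Then make the Abstract and the section Study design and population consistent with the result.

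This costs one rerun and some wording, and no additional children. The stated power becomes less favourable. The restatement makes the claim honest but does not raise the power.

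If the authors find that 268 was meant as the per-arm output, they should say so. That would mean 536 children in total, twice the planned enrolment, and by the t calculation it would still give about 76%. It is therefore a change of design, not a correction of wording.
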